## 8.4 Endpoints

### 8.4.1 Primary endpoint

The change in the proliferation of normal breast epithelium with UA treatment, assessed as the percentage of epithelial cells staining positively for nuclear Ki67 before and on treatment.

### 8.4.2 Secondary endpoints

Secondary endpoints are the change in the relevant outcome with UA therapy across the whole population of participants:

- Percentage of luminal, basal and mixed colonies by morphological analysis of adherent feeder layer assay
- Percentage of luminal progenitor cells (EPCAM+/CD49f+) by FACS analysis
- Tissue stiffness assessed as the reduced indentation modulus by atomic force microscopy
- Mean tissue section percentage fibrillar collagen assessed by picrosirius red staining and polarised light microscopy
- Background parenchymal enhancement assessed by magnetic resonance imaging (MRI)
- The side effect profile of UA in this patient population assessed by CTCAE v4.03

- The relative change in Ki67 with UA treatment between those with and without known mutation in BRCA1/2 genes

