### **2.2. Progesterone and the human breast**

In the normal human breast the two PgR isoforms (PRA and PRB) are co-expressed at comparable levels. Relative loss of PRB is seen with the development of atypia or malignancy and in women with germline mutations in BRCA1 or 2 (Mote 2002). Women with such mutations have double the serum progesterone levels compared to age matched wild-type controls (Widschwendter 2013). The combination of estrogen and progestin as hormone replacement therapy (E+P HRT) significantly increases BC incidence and mortality whereas estrogen alone (E-HRT) does not (Anderson 2004; Chlebowski 2003; Chlebowski 2010; Beral 2003). In premenopausal women breast epithelial cell proliferation is highest in the progesterone dominant luteal phase of the menstrual cycle and can be reduced by the antiprogestin mifepristone, although this drug has now been discontinued due its hepatic toxicity (Engman 2008; Potten C 1988; Pike 1993; Navarrete 2005).

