## **9.5 Exploratory analyses**

### **Gene expression**

To determine gene expression using unbiased methods before and after treatment, fresh frozen tissue from patients will be subject to RNA extraction and Poly(A) RNA-Sequencing and analysed using appropriate BioConductor packages to identify pathways and key nodes perturbed by UA. Validation of expression changes in selected individual genes will be performed using qRT-PCR and IHC. Further fresh frozen tissue will be stored for future DNA analysis. Germline moderate/high risk genes will be sequenced and BC risk SNPs profiled using oncoarrays.

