## 10 Statistical considerations

In a previous study using mifepristone and FNA of the normal breast (Engman 2008) a significant reduction in Ki67 was seen with only 8 patients in the treatment group ( $5.76 \pm 1.42$  vs  $0.79 \pm 0.27$   $p=0.012$ ). In contrast no difference was seen in 6 placebo treated women. A 30 subject study will thus provide sufficient subjects to explore variability in response both by primary endpoint (Ki67) but also secondary clonogenic, stromal and radiological endpoints. We will seek to recruit approximately half of the group with and half without BRCA mutations given the potential differential sensitivity in luminal progenitors described above.

Differences between baseline and on treatment Ki67 ( $\Delta$ Ki67) across the whole population (primary endpoint analysis) will be assessed using the Wilcoxon signed rank test. Differences in  $\Delta$ Ki67 between women with and without known BRCA mutations and other exploratory analyses (such as development of amenorrhoea vs not and sample dichotomised by median age and on treatment progesterone levels) will be assessed using the Mann-Whitney U-test.

Secondary endpoint analyses will be conducted in a similar manner using the relative expression levels of individual genes by qRT-PCR ( $\Delta$ CT value) or proteins by immunohistochemistry using percentage cells staining positively before and after therapy (for individual proteins this may be in the nucleus, cytoplasm, cell membrane or combination of these as appropriate); semiquantitative analysis of fibrillar collagen by picrosirius red staining and the proportion of luminal progenitors in clonogenic and FACS analyses (CD49f+/EPCAM+). The categorical Bi-RADs values for MRI scans will be analysed using appropriate non-parametric tests.

As one of the primary aims of the study is to identify imaging biomarkers of anti-progestin activity we will classify MRI changes according to reduction in background parenchymal enhancement (BPE) with UA treatment. Serial MRI studies demonstrate moderate to marked reduction in BPE in 50% of women transiting menopause and a similar proportion with increased BPE in the luteal vs follicular phase of the menstrual cycle. As BPE is associated with BC risk we hypothesise that any reductions in BPE with UA will correlate with reduced BC risk. We will correlate UA induced changes in BPE (and also FGV and ADC) with changes in clonogenicity and proportion of cells in each compartment (basal, luminal

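### The BRCA secondary endpoint is named as a relative change in Ki67 but tested on unadjusted absolute differences, so a baseline difference between the groups could pass for a difference in response

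*Protocol*

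**What the plan says.** Ki67 is measured as a percentage of cells: Section 8.4.1 has it "assessed as the percentage of epithelial cells staining positively for nuclear Ki67 before and on treatment". Among the secondary endpoints, Section 8.4.2 lists "The relative change in Ki67 with UA treatment between those with and without known mutation in BRCA1/2 genes".

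Section 10 introduces ΔKi67 for the primary analysis as "Differences between baseline and on treatment Ki67", which is a quantity in percentage points. It then carries the same ΔKi67 into the comparison "between women with and without known BRCA mutations and other exploratory analyses", which "will be assessed using the Mann-Whitney U-test". For this contrast it states no ratio, percentage change, log scale or baseline covariate.

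The planned size is 30 women, about half of them carriers. The justification is general: "A 30 subject study will thus provide sufficient subjects to explore variability in response". No power or significance level is given for the BRCA comparison.

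**The concern.** A relative change and a difference in percentage points are different quantities. If two groups start at different Ki67 and lose the same proportion of it, the relative change shows no BRCA effect while the absolute differences do diverge. A significant Mann-Whitney result on ΔKi67 could then reflect the starting level rather than sensitivity to treatment.

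The protocol's background makes unequal starting levels plausible. Section 2.2 says "Women with such mutations have double the serum progesterone levels compared to age matched wild-type controls" and adds that epithelial proliferation peaks in the luteal phase, which is when the baseline biopsy is taken. Differential sensitivity of carriers is also the stated reason for seeking an even split by BRCA status, so the contrast should be able to address it.

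**Working it through.** **Inputs from Section 10.** Ki67 of 5.76 ± 1.42 before and 0.79 ± 0.27 on mifepristone, 8 treated women, p = 0.012; 30 women, taken as 15 against 15.

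**The plan's own figures.** The total of 30 cannot be reproduced, because no effect size, SD of change, significance level or power is given. The cited p-value can be checked if a signed-rank test with all 8 changes in one direction is assumed: z = 18/√(8×9×17/24) = 18/√51 = 2.52, two-sided p = 0.0117, which agrees with 0.012.

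**Arithmetic of the two scales.** The cited fall is 1 − 0.79/5.76 = 86.3%. Applied to a baseline of 5.76 it leaves 0.79, a drop of 4.97 points. Applied to twice that baseline, 11.52, it leaves 1.58, a drop of 9.94 points. The relative change is identical and the absolute change doubles.

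**Spread of baseline Ki67.** The protocol does not say whether ± is an SD or a standard error. As an SD, the coefficient of variation (CV) is 1.42/5.76 = 0.25. As a standard error, it is 1.42×√8/5.76 = 4.02/5.76 = 0.70.

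**Assumptions not in the documents.** Lognormal baselines; carrier to non-carrier baseline ratio of 1 to 2; between-woman CV of 0.5 in the response; two-sided 5% level; baseline measured without error.

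**Simulation.** 15 against 15, at least 4,000 trials per setting (simulation standard error at most √(0.25/4000) = 0.8 points). No trial has a BRCA effect at a given baseline. Three response models were used: on-treatment Ki67 proportional to baseline, falling to a common floor (mean 0.79), or proportional to the square root of baseline. Entries are the share of trials declaring a BRCA difference; ranges at ratios 1.5 and 2 run from CV 0.70 to CV 0.25.

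| Response, same in both groups | Test | Ratio 1 | Ratio 1.5 | Ratio 2 |
|---|---|---|---|---|
| Proportional, 86% fall | Mann-Whitney, absolute difference (as planned) | 4–5% | 36–98% | 78–100% |
| Proportional, 50% fall | Mann-Whitney, absolute difference (as planned) | 4–5% | 22–51% | 52–88% |
| Proportional, either fall | Mann-Whitney, log ratio | 4–5% | 4–5% | 4–5% |
| Common floor | Mann-Whitney, log ratio | about 5% | 23–46% | 63–91% |
| Square root | Mann-Whitney, log ratio | about 5% | 14–17% | 33–43% |
| All of the above | Log on-treatment regressed on log baseline plus BRCA group | near 5% | near 5% | near 5% |

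**Sensitivity of the planned test.** At a ratio of 1.25 with an 86% fall it rejects in 14% (CV 0.70) to 57% (CV 0.25). A CV of 1.0 gives 23% at 1.5 and 55% at 2. Counting noise on 1,000 cells, the minimum that Section 9.1 aims for, gives 34% and 77% at CV 0.70. Setting the median rather than the mean response ratio to 0.5 lowers the 50%-fall ranges to 17–39% and 41–72%.

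**Why the regression is still on the relative scale.** log(T) = a + b·log(B) + c·BRCA is the same model as log(T/B) = a + (b − 1)·log(B) + c·BRCA. So exp(c) compares the on-treatment to baseline ratio of carriers and non-carriers at the same baseline. The plain log-ratio comparison fixes b at 1. That explains why it is correct under a proportional response and fails under the other two.

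**The case against.** The wording in Section 8.4.2 can be read loosely as the change in one group relative to the other, which is close to what Section 10 tests. That reading is possible, and it is one reason to ask for reconciliation rather than to call the test plainly wrong. It still leaves the scale unsettled.

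A reader might infer that carriers will start at higher Ki67 and that a false BRCA effect is therefore to be expected. The documents do not support this. They give no Ki67 by BRCA status and no relation between progesterone level and Ki67. Section 8.1 also requires every woman to be in a confirmed ovulatory luteal phase, so the luteal versus follicular contrast does not separate the groups. All the inflation comes from the assumed ratio; at equal baselines there is none. The highest figures also need the cited ± to be an SD.

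Nor does the planned test measure only the starting level. It also responds to a true difference in response, and where baselines differ the absolute falls do differ. The result misleads only as an answer about relative change.

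Section 10 places this contrast alongside exploratory analyses in a small pilot, and an analysis plan, not shown, could add detail. That lowers the importance. It does not remove the conflict, because the protocol itself fixes two different scales.

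One might also object that women without a known mutation may include untested carriers, although "Germline moderate/high risk genes will be sequenced and BC risk SNPs profiled using oncoarrays". This is a side point. Under Section 7.1 the germline sample is optional and is taken after visit 4, so it cannot classify everyone.

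**Conclusion.** The point holds at moderate importance. Sections 8.4.2 and 10 define the BRCA contrast on different scales, nothing else in the protocol reconciles them, and the stated test has no protection against a baseline difference. If carriers started 1.5 times higher, an identical proportional response would be declared a BRCA difference in about 36% to 98% of trials with an 86% fall, and in 22% to 51% with a 50% fall. At twice the baseline the ranges are 78% to 100% and 52% to 88%. These figures rest on the assumed baseline ratio and on lognormal data with baseline CV 0.25 to 0.70; a wider spread lowers them.

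It would go too far to conclude that the trial's main result is at risk. The signed-rank test on ΔKi67 matches the primary endpoint in Section 8.4.1. It would also go too far to treat a simple log-ratio test as an adequate replacement, since it fails in the same way if both groups fall towards a common floor.

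**What to change.** Reword Sections 8.4.2 and 10 so that both describe the BRCA contrast on the relative scale. Specify the analysis as a regression of log on-treatment Ki67 on log baseline Ki67 plus BRCA group, reporting exp(c) with its confidence interval. Fix the offset for zero counts before the sample time points are unblinded. Keep the Mann-Whitney comparisons of the absolute difference and of the log ratio as supportive only, and do not present the log ratio as equivalent to the adjusted model. Optionally, add a sensitivity analysis that takes BRCA status from the trial's germline result where a woman has one.

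The cost is a few sentences and no new data, since baseline Ki67 is already collected for the primary endpoint. The downside is one model assumption and one offset choice in a 30-woman pilot. Adjustment also removes a baseline difference only as far as baseline Ki67 is measured well; noise from a small tissue sample would leave some of it, which the report should acknowledge.

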## 8.5 Exploratory endpoints

The changes in expression of individual genes and key pathways induced by UA therapy

The changes in key stem cell and PgR target proteins induced by UA therapy

The changes in fibroglandular volume and other MRI/US elastography biomarkers

The changes in fibroglandular and fat tissue stiffness assessed by ultrasound elastography and acoustic radiation force imaging (ARFI)

The changes in breast impedance measured at baseline and 3 months.

## 9 Specific protocols for endpoint analyses

### 9.1 Ki67 analysis

Samples will be transported to the Breast Biology Group laboratories in 10% formalin. After 24+/-6 hours in formalin (and with the exact time documented) samples will be embedded in paraffin in the pathology core facility at the CRUK Manchester Institute (CRUK-MI). Samples will be embedded in optimal cutting temperature cryo-sectioning media and snap frozen into a 2.5cm mould with liquid nitrogen cooled isopentane. Frozen sections (5um) will be cut at -20°C, air dried, washed in distilled H2O and stored at 4°C prior to use.

Paraffin sections will undergo antigen retrieval at 115 °C for 3 min (microwave processor) in Tris-EDTA buffer (pH 9.0) followed by staining with anti-MIB1 antibody at 1:200 dilution for 1 hour incubation at 37 °C. Following appropriate and uniform secondary antibody application and signal amplification the slides will be manually scored with the operator blinded to the sample time point (baseline or on treatment). For final analysis all samples will be stained and analysed at the same time to avoid between batch variability. However, local optimisation of the techniques using some of the samples may occur prior to this. The operator will count at least 1000 cells per sample where possible and score the percentage with nuclear Ki67 staining.

### 9.2 Clonogenic assays

Clonogenicity will be assessed through adherent feeder layer and suspension mammosphere assays in unsorted cells. For adherent clonogenic assays mammary cells (2,000-5,000 cells) from individual patients will be plated with irradiated fibroblasts (a generous gift from our collaborator [name], Cambridge) and cultured in SF7 medium containing 5% FBS + 20uM ROCK inhibitor at 5% oxygen conditions for 7-10 days. Colonies will be fixed and typed (basal/luminal/mixed) by morphological analysis as previously described (Clarke 2005, Eirew 2010). FACS analysis will be performed on freshly isolated single cell suspensions (~200-300,000 cells) by first excluding lineage+ cells (CD45 – haematopoietic, Ter119 –erythrocytes, CD31 – endothelial), and then identifying the

proportion of basal cells (CD49f+/EPCAM-/lo), luminal progenitor cells (CD49f+/EPCAM+) and differentiated luminal cells (CD49f-/EPCAM+) before and after therapy with UA.

### 9.3 Morphological analysis, tissue stiffness and collagen analyses

Samples will be transported to the Breast Biology Group laboratories in 10% formalin. After 24+/-6 hours in formalin (and with the exact time documented) samples will be embedded in paraffin in the pathology core facility at the CRUK Manchester Institute (CRUK-MI). Samples for morphological analysis will be transferred to the MFT pathology laboratories. Samples for stromal/collagen analyses will be transported to the laboratory of [name] in the Faculty of Life Sciences, The University of Manchester.

H&E sections will be assessed by an accredited pathologist for evidence of invasive cancer or DCIS. Any changes will be investigated further using additional samples and more conclusive testing as per standard routine practice.

#### Tissue stiffness

Micro-indentation of peri-ductal breast tissue will be carried out using a Bioscope Catalyst AFM (Bruker, Coventry, UK) mounted onto an Eclipse T1 inverted optical microscope (Nikon, Kingston, UK) fitted with a spherically tipped cantilever (nominal radius and spring constant of 1µm and 3N m^-1 respectively: Windsor Scientific Ltd., Slough, UK,) running Nanoscope Software v 8.15 (Bruker, Coventry, UK). The local reduced modulus will be determined for each of 400 points in a 25x25µm region, indented at a frequency of 1 Hz with lateral spacing of 1.25 µm. The extend curve will be used in conjunction with a contact point based model to calculate the reduced modulus for each indentation. For each biological sample, three 25µm^2 regions and hence 1200 force curves will be collected. A baseline correction will be applied to each curve before a force fit is applied using trh Herzian (spherical) model and a maximum force fit of 70%. Once all 400 force curves have been generated, a quality control will be applied whereby any force values falling more than two standard deviations away from the mean value will be discarded in order to account for failed indents (Crick 2007; Graham 2010).

#### Collagen analysis

FFPE samples (see above) will be stained with picosirius red (PSR) for a 1 hour incubation with 0.1% sirius red F3BA in saturated aqueous picric acid at pH 2 followed by clearing in 0.1% acetic acid, dehydration and mounting in DPX (Graham 2011). When visualised under cross-polarised light, the resultant collagen-associated birefringence will be assessed semi-quantitatively against total tissue area.

### 9.4 Magnetic Resonance Imaging

Previous studies have demonstrated rapid reductions in background parenchymal enhancement (BPE) with SERM therapy in premenopausal women and greater reduction in BPE than FGV with transition from pre- to post-menopausal. We hypothesise that BPE will

also reduce in women sensitive to the effects of the antiprogesterin UA with three months of treatment. The primary imaging analysis will, therefore, be the change in BPE associated with UA therapy within individuals, scored according to the BI-RADS categories (minimal, mild, moderate and marked).

## **9.5 Exploratory analyses**

### **Gene expression**

To determine gene expression using unbiased methods before and after treatment, fresh frozen tissue from patients will be subject to RNA extraction and Poly(A) RNA-Sequencing and analysed using appropriate BioConductor packages to identify pathways and key nodes perturbed by UA. Validation of expression changes in selected individual genes will be performed using qRT-PCR and IHC. Further fresh frozen tissue will be stored for future DNA analysis. Germline moderate/high risk genes will be sequenced and BC risk SNPs profiled using oncoarrays.

### **Immunohistochemistry and tissue microarray (TMA)**

Cores will also be taken from the FFPE samples to construct a tissue microarray (TMA). Staining of the TMA will be performed in accordance with validated protocols for known regulators of PgR action (ER, PRA/B ratio, RANKL and Wnt4) and stem cell function (ALDH1a1 and 1a3, Notch-1 and Notch 4-ICD, Hes1 and Hey2, Lef1, Axin2, Lgr4/5 and nuclear beta catenin). These parameters will be analysed in both the epithelial and stromal cell populations in tissue sections. Baseline and dynamic change in subnuclear localisation of PR with UA will be examined as a biomarker of antiprogesterin activity (Scarpin 2009). To investigate the effects of UA on matrix composition expression of collagen, proteoglycans, focal adhesion complex signals (eg paxilin and phospho-FAK) will be assessed.

### **Imaging**

MRI has the advantage that, unlike mammography, it can be repeated early in the course of treatment as it does not use ionising radiation. It is crucial that the biological correlates of these imaging data are examined in detail in this and future prevention studies. We will seek to develop an objective standardised method for assessment of BPE to be taken forward to future large scale assessments of risk in the national high risk screening programme. This will include correlation of visually assessed and ROI-based measures of BPE with the other factors. We also propose to measure the apparent diffusion coefficient (ADC) which reflects the freedom of movement of water molecules within the tissue and is related to tissue cellularity and water content. There is a paucity of data on changes in ADC in response to hormonal therapy, but ADC values are lower in post-menopausal women (O'Flynn 2012) and one study has reported small changes during the menstrual cycle (Partridge SC 2001). Diffusion tensor imaging will give ADC directional information (fractional anisotropy).

Ultrasound elastography will also be performed immediately prior to the vacuum biopsies. This will be with a Siemens S3000 ultrasound machine utilising acoustic radiation force imaging (ARFI) with a 9Mz probe. Measurements of fibroglandular and fat tissue stiffness will be performed in each of the four quadrants of both breasts, targeting the densest and least

dense area in each quadrant respectively. Changes in tissue stiffness between pre- and post-treatment scans will be explored and correlated with the MRI data.

## Blood

Both serum and plasma samples will be taken and stored for subsequent analysis at baseline and 12 week time points ie when bloods are already being taken, to prevent additional venepunctures. The precise analyses to be performed are not known at this time, however, the storage of both serum and plasma will facilitate detailed hormonal and proteomic analyses. 10ml serum samples will be prepared in standard tubes. Plasma samples will be collected in EDTA tubes and spun at 2000rpm for 10 minutes at room temperature before storage at -80°C in the on-site Nightingale Centre -80°C freezer (MFT).

## 10 Statistical considerations

In a previous study using mifepristone and FNA of the normal breast (Engman 2008) a significant reduction in Ki67 was seen with only 8 patients in the treatment group ( $5.76 \pm 1.42$  vs  $0.79 \pm 0.27$   $p=0.012$ ). In contrast no difference was seen in 6 placebo treated women. A 30 subject study will thus provide sufficient subjects to explore variability in response both by primary endpoint (Ki67) but also secondary clonogenic, stromal and radiological endpoints. We will seek to recruit approximately half of the group with and half without BRCA mutations given the potential differential sensitivity in luminal progenitors described above.

Differences between baseline and on treatment Ki67 ( $\Delta$ Ki67) across the whole population (primary endpoint analysis) will be assessed using the Wilcoxon signed rank test. Differences in  $\Delta$ Ki67 between women with and without known BRCA mutations and other exploratory analyses (such as development of amenorrhoea vs not and sample dichotomised by median age and on treatment progesterone levels) will be assessed using the Mann-Whitney U-test.

Secondary endpoint analyses will be conducted in a similar manner using the relative expression levels of individual genes by qRT-PCR ( $\Delta$ CT value) or proteins by immunohistochemistry using percentage cells staining positively before and after therapy (for individual proteins this may be in the nucleus, cytoplasm, cell membrane or combination of these as appropriate); semiquantitative analysis of fibrillar collagen by picrosirius red staining and the proportion of luminal progenitors in clonogenic and FACS analyses (CD49f+/EPCAM+). The categorical Bi-RADs values for MRI scans will be analysed using appropriate non-parametric tests.

As one of the primary aims of the study is to identify imaging biomarkers of anti-progestin activity we will classify MRI changes according to reduction in background parenchymal enhancement (BPE) with UA treatment. Serial MRI studies demonstrate moderate to marked reduction in BPE in 50% of women transiting menopause and a similar proportion with increased BPE in the luteal vs follicular phase of the menstrual cycle. As BPE is associated with BC risk we hypothesise that any reductions in BPE with UA will correlate with reduced BC risk. We will correlate UA induced changes in BPE (and also FGV and ADC) with changes in clonogenicity and proportion of cells in each compartment (basal, luminal

progenitor and luminal). Similarly, any changes in stromal composition, organisation or stiffness assessed by AFM will be correlated with changes in MRI parameters.

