## 5.4 Drug storage, supply and labelling

### 5.4.1 Dosing Regimen

An oral dose of ulipristal acetate of 5 mg daily was chosen because this drug is only available in oral form and this is an effective dose which induces anovulation in 70-80% of women and a significant fall in serum progesterone. This makes it a suitable test dose for this pilot study.

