### 6.1. Inclusion Criteria

- Premenopausal females aged between 25 and 45 years
- Regular menses defined as date of onset of last menstrual period +/- 3 days of expected
- Willing to use an acceptable method of contraception from screening to 2 weeks after study drug discontinuation (see Restrictions section 5.3 below)
- Known BRCA1 or BRCA2 mutation or moderate to high risk of developing BC defined as >17% lifetime risk from age 20 or >3% risk between 40-50 years
- Ovulatory menstrual cycles defined as serum progesterone  $\geq 15\text{nmol}$  in the luteal phase of the menstrual cycle (2 weeks prior to expected onset of menses).

- Willing and able to provide informed consent to undergo all trial procedures.

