### **Visit 3 Day 78-85 (week 12)**

During this visit the participants will:

- be asked if they are happy to continue in the trial. and the importance of using contraception throughout the trial will be emphasised.
- have blood samples taken for serum progesterone, APTT/PT/FBC/U+E/LFTs of which bilirubin, ALT, ALP and LDH will be recorded /LDH, lipid profile and TFT. If ALT is more than three times the upper limit of normal, UA must be permanently discontinued Research samples will also be taken for storage.
- have their samples prepared and stored as described in sections 8 and 9
- have any changes to their concomitant medications documented
- have a urine pregnancy test performed
- have their weight recorded
- have any adverse events documented and be asked whether they have had any vaginal bleeding.
- have a drug accountability check performed

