## **8 Methodology**

### **8.1 Timing of study entry by luteal phase progesterone**

Luteal progesterone levels will be checked 7 days prior to the expected onset of the next menstrual cycle. The serum progesterone level must be  $\geq 15\text{nmol}$  to confirm an ovulatory menstrual cycle for further trial related procedures to take place. If the level is  $< 15\text{nmol}$  then one further measurement may be taken in the following menstrual cycle (again at day 7 prior to expected onset of menses). If the progesterone level on the second occasion is  $< 15\text{nmol}$  then screening has failed and the woman will not be permitted to enter the study.

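### Exploratory analyses cut age and, on the natural reading, on-treatment progesterone at the sample median, which loses power that a rank correlation would keep at no cost

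*Protocol*

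**What the plan says.** Section 10 tests the primary endpoint, the Ki67 change in the whole group, with the Wilcoxon signed rank test. It then lists the comparison by BRCA status and "other exploratory analyses (such as development of amenorrhoea vs not", followed by the "sample dichotomised by median age and on treatment progesterone levels) will be assessed using the Mann-Whitney U-test". No cut other than the median is named. The sample size is justified in the same section: "A 30 subject study will thus provide sufficient subjects to explore variability in response".

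Three other places bear on this.

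- Section 5.4.1, on UA 5 mg daily: "this is an effective dose which induces anovulation in 70-80% of women and a significant fall in serum progesterone".
- Section 7.1, Visit 3 (day 78-85), schedules the only on-treatment progesterone sample: "have blood samples taken for serum progesterone, APTT/PT/FBC/U+E/LFTs of which bilirubin, ALT, ALP and LDH will be recorded". The telephone-call entry in the same section counts day 1 from the first dose.
- Sections 6.1 and 8.1 set an ovulatory threshold of 15 nmol for a luteal-phase sample. Section 8.1 uses it "to confirm an ovulatory menstrual cycle for further trial related procedures to take place". It serves eligibility only.

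**The concern.** Age (Section 6.1: "Premenopausal females aged between 25 and 45 years") and serum progesterone are both continuous. A median split treats all women on one side of the cut as alike and exaggerates the contrast between neighbours on either side of it. In a sample of 30 the loss is material.

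For progesterone the position of the cut also matters. If most women are anovulatory on treatment, the sample median falls among the anovulatory women. The upper half then holds the ovulating women together with anovulatory women placed there by small differences in low values. A real difference in Ki67 response between ovulating and anovulatory women would be diluted, and a null result could be misread as no relation to progesterone. Exploring variability in response is part of the stated case for 30 women, so a weak method for it has a cost even in a pilot.

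**Working it through.** **Inputs.** N = 30 (Section 10); anovulation 70-80% (Section 5.4.1). The protocol gives no alpha, effect size or power for these tests, so there is no planned figure to reproduce. Assumed: two-sided 5%, all 30 women evaluable, correlations of 0.3 to 0.6, and ovulatory-anovulatory differences of 1.0 or 1.5 SD in Ki67 change.

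**1. Cost of the split for a continuous relation.** Bivariate normal data with n = 30 were simulated. The median split with Mann-Whitney was compared with Spearman on the uncut values.

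| True correlation | Median split | Spearman | Loss (points) |
|---|---|---|---|
| 0.3 | 23% | 34% | 11 |
| 0.4 | 37% | 55% | 18 |
| 0.5 | 55% | 77% | 22 |
| 0.6 | 76% | 92% | 16 |

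Repeat simulations agree to within about 3 points. As a large-sample check, a median split of a normal variable has efficiency 2/π = 0.64 against the uncut variable. The split therefore uses the information of about 30 × 0.64 = 19 women.

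**2. Make-up of the upper progesterone half.** This takes the median as the progesterone cut, and takes the case kindest to the split, in which every ovulating woman ranks above every anovulatory woman.

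- At 70% anovulation: 30 × 0.70 = 21 anovulatory and 9 ovulating. The upper half holds 9 ovulating and 15 − 9 = 6 anovulatory women (6/15 = 40%).
- At 80% anovulation: 30 × 0.80 = 24 anovulatory and 6 ovulating. The upper half holds 6 ovulating and 15 − 6 = 9 anovulatory women (9/15 = 60%).

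**3. Dilution.** Let D be the ovulatory-anovulatory difference in mean Ki67 change, with no relation to progesterone within either group. The lower half is wholly anovulatory, so the expected difference between halves is D × (ovulating women in the upper half)/15. That is 9/15 = 60% of D at 70% anovulation and 6/15 = 40% of D at 80%.

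**4. Power under that two-group model**, with every ovulating woman's sample showing her status.

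| Ovulating women | Difference | Median split | Grouped by true ovulatory status |
|---|---|---|---|
| 9 | 1.0 SD | 30% | 63% |
| 9 | 1.5 SD | 51% | 94% |
| 6 | 1.0 SD | 14% | 50% |
| 6 | 1.5 SD | 22% | 86% |

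At 1.5 SD, Spearman gives about 46% with 6 ovulating women and about 75% with 9. It beats the median split here too.

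**5. How far the 15 nmol cut can be trusted on treatment.** The last column of step 4 needs every ovulating woman to be sampled in her luteal phase. Sections 6.1 and 8.1 define the threshold for such a sample. The day 78-85 sample is timed from the first dose, and Section 5.6.3 expects menses to be delayed or to stop. If only half of the ovulating women happen to be luteal at sampling, power at the 15 nmol cut for a 1.5 SD difference falls to about 44-51%.

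**The case against.** The strongest reply is that little hangs on this. The splits are examples in a parenthesis of exploratory analyses. Neither age nor progesterone is a listed endpoint, nothing forbids a further continuous analysis, and the same sentence already plans a comparison by amenorrhoea, which is a natural grouping related to ovarian suppression. All of that stands and limits the weight of the point. It does not make the median split a good choice: Section 10 names that method, and a better one costs nothing.

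The wording is also open. Median may govern age alone, which would leave the progesterone cut unspecified. Then steps 2 to 4 do not apply to the plan as written. A median cut for both is still the natural reading, since no other is given.

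Two stronger readings are tempting and not supported. A reader might infer that loss of ovulation is the trial's main mechanistic question. Section 3 frames the hypothesis around progesterone receptor signalling and the aims around tissue effects and imaging biomarkers; anovulation appears only in the dose rationale and the note on pregnancy risk. A reader might also infer that regrouping at 15 nmol would bring power to the levels in the last column of step 4. That assumes perfect luteal timing, which the visit schedule does not provide, and an effect driven wholly by ovulatory status.

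**Conclusion.** The point holds as a modest one. For a continuous relation, the median split gives up roughly 11 to 22 percentage points of power against Spearman at n = 30. For progesterone, if the median is the cut, 40-60% of the upper half would be anovulatory on the protocol's own figure, and a true difference would appear at about 40-60% of its size.

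The counts and the dilution follow from the protocol's 70-80% and a cut at one half. The power figures rest on assumed effect sizes, normal data and all 30 women being evaluable. For age, only the general cost of dichotomising applies. The finding should not be read as a threat to the trial's main result: the Wilcoxon test of the whole group and the BRCA comparison are untouched.

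**What to change.** In Section 10, replace the median splits with Spearman correlation, or a rank regression, of the Ki67 change on age and on on-treatment progesterone, each kept continuous. This also removes the doubt about what median governs. The section already plans correlations for the imaging, cell and stromal changes, so the method is in keeping with the plan.

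A comparison of women at 15 nmol or more with those below may be shown as a supplement only. It should carry the caveat that the threshold is defined for a luteal-timed sample while the day 78-85 sample is timed from the first dose, so some ovulating women would be classed as anovulatory.

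The cost is a change of wording. Visits, samples, sample size and the primary analysis stay as they are.
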